# **List of Abbreviations**

| VUMC | Vanderbilt University Medical Center |
| --- | --- |
| CPPE | Complicated parapneumonic pleural effusion |
| RCTs | Randomized controlled trials |
| BTS | British Thoracic Society |
| tPA/DNase | Intrapleural tissue plasminogen activator and dornase alfa |
| LDH | Lactate dehydrogenase |
| VATS | Video-assisted thoracoscopic surgery |
| CRF | Case report form |
| REDCap | Research Electronic Data Capture |
| DAGs | Data Access Groups |
| AE | Adverse event |
| SAE | Serious adverse event |

# **Objectives**

The primary objective of this study is to evaluate the impact of regular chest tube flushing on the length of time to catheter removal for patients admitted with an infected pleural space who require thoracostomy for the management of a complicated parapneumonic pleural effusion (CPPE) and/or empyema.

The secondary objective of this study is to evaluate the impact of regular chest tube flushing on the length of total hospitalization for patients, radiographic improvement on chest imaging, the need for additional pleural interventions, and associated complications of chest tube management. We will employ ordinal multi-state transition modeling to analyze the magnitude of the intervention’s impact on successful or failed outcomes over the course of the chest tube dwell period.

# **Rationale**

There are no randomized controlled trials (RCTs) evaluating the role of regular chest tube flushing in the setting of pleural space infection for optimal drainage and treatment outcomes. Most studies of <16 Fr catheters have used both flushing and suction to decrease the likelihood of catheter blockage and improve drainage efficiency, however, this practice has never been studied prospectively or in RCTs. Regular flushing (e.g., 20-30 ml saline every 6 h via a three-way stopcock) is recommended for small chest drains by the British Thoracic Society (BTS) 2010 Guidelines and not addressed in the most recent 2023 guidelines. Regular flushing is followed variably by some and not used by others. Importantly, the role of this practice in successful drainage of infected fluid, and patient-centric outcomes has not been investigated. Inconsistent flushing practices confound the interpretation of therapeutic modalities (such as tPA/DNase) success or lack thereof and limit the execution of RCTs and prospective studies of the pleural space in the setting of infection.

# **Background**

Pleural effusions are a frequent complication of acute pulmonary infections and can impact patient morbidity and mortality (Sorino). For example, of those hospitalized with pneumonia, 20% to 40% have a parapneumonic effusion, and 5% to 10% of these parapneumonic effusions progress to empyema with approximately one-third of patients requiring surgical drainage of the pleural space (Najafi, Shen). Based on the 2016 National Hospital Care Survey, nearly 77,000 adult patients were hospitalized for pneumonia with 35% of inpatients dying either in the hospital or within 1 year of discharge (Peters). Those with pleural space infections often require additional procedures with increased length of hospital stay.

The three stages of parapneumonic pleural effusion include (1) simple exudative accumulation (2) fibropurulent with bacterial invasion of the pleural cavity, and finally, (3) the organized stage with the formation of scar tissue (Sorino). A parapneumonic effusion in the fibropurulent stage is usually defined as “complicated” since antibiotic therapy alone is not sufficient for its resolution and an invasive procedure (pleural drainage or surgery) is required. Biochemical features of a fibrinopurulent collection include a low pH (<7.2), low glucose level (<60 mg/dl), and high lactate dehydrogenase (LDH). Empyemas are often defined as frank pus aspirated from the pleural space, with some further defining positive gram stain and/or culture positivity as empyemas (Shen, Light, Davies).

The most recent BTS guidelines recommend that patients with frankly purulent, turbid/cloudy pleural fluid, or with a pH <7.2 on sampling should receive prompt pleural space chest tube drainage, although there is no consensus on optimal thoracostomy size in the absence of a randomized controlled trial (Davies). In a subanalysis of the Multicenter Intrapleural Sepsis Trial (MIST1) cohort, there was no increased efficacy with large-bore tubes compared with small-bore drains (Maskell).

One criticism of the use of smaller bore chest tubes for pleural infection management is the risk of drain obstruction which could be ameliorated through flushing of the catheter with sterile saline. The BTS guidelines recommend regular flushing (20–30 ml saline every 6 h via a three-way tap) for smallbore catheters and the application of suction (−20 cm H2O) in the hopes of improved drainage (Davies). However, there is no RCT evaluating these drain management issues, including flushing and drain suction.

In the observational retrospective study by Cafarotti et al., ninety-seven 12F drains were placed for empyemas with 62.8% of drains were ultimately removed secondary to blockage, often with observed fibrin or blood in the drain. Drain flushing was performed with 50 mL of saline solution in case blockage was suspected (Cafarotti). Similarly, a retrospective review of one hundred 12F chest tubes (20% placed for pleural infections) found that 9% of the drains became blocked (Davies). However, 58 catheters were flushed regularly with 20 ml of sterile saline every 6 hours, and found that the frequency of drain blockage in pleural effusion was reduced by administration of regular normal saline drain flushes (odds ratio for blockage in flushed drains compared with non-flushed drains 0.04, 95% CI: 0.01–0.37, p<0.001) (Davies). Additionally, there appears to be support for the addition of saline flushing when administering intrapleural lytic therapy with less overall doses of fibrinolytics needed in the group of patients receiving saline (and no adverse events attributed to saline therapy) (Porcel).

These findings are not consistent across all studies. Horsley et al. prospectively analyzed 52 catheters (ranging from size 12-20F) and found that 6 of the 10 drains placed for empyema management were complicated by blockage. Regular flushing with 30 mL saline four times daily was used in the clogged drains and in an additional five chest tubes that did not block. Flushing drains with saline solution did not appear to alter the chance of blockage (Horsley). Many centers within and outside the US, do not follow regular flushing protocols and instead, evaluate for blockage and only flush if a catheter appears blocked and non-draining. This is further supported by studies of pleural space infection that do not report a chest tube flush protocol. As a result, the speculation of “flush role in the outcome and successful chest tube removal” is the standard study limitation listed in most pleural space infection studies.

This inconsistency in prior literature and the absence of RCTs for optimal drain management has led to variability in practice despite the BTS 2010 guidelines. We propose a multicenter trial evaluating the utility of regular chest drain flushing of catheters placed for the management of pleural space infection.

# **Hypothesis**

Regular thoracostomy flushing of catheters placed for the management of pleural space infection leads to earlier successful chest tube removal. This, in turn, may lead to improved overall outcome measures such as earlier discharge from the hospital, optimal resolution of pleural space infection, prevention of surgical management, or additional invasive procedures in the pleural space (such as additional drains).

# **Design**

This study will be a multicenter, open label randomized controlled trial.

# **Study Population**

All consecutive patients with a pleural space infection requiring chest tube placement for inpatient management will be screened for study inclusion.

# **Study Criteria**

**Inclusion Criteria**

- Patients with CPPE and empyema requiring chest tube placement as standard of care for inpatient management of their pleural space infection with or without intrapleural tPA/DNase therapy
- Age > 18 years old.

**Exclusion Criteria**

• Chest tube has been in situ >24 hours.

• Patients who have chest tubes that can’t accommodate a three-way stopcock.

• Chest tube is an indwelling tunneled pleural catheter.

• Study subject has any disease or condition that interferes with the safe completion of the

study.

• Inability to provide informed consent.

• If the managing clinician believes the chest tube will be placed for less than 24 hours.
• Patients admitted with an indwelling chest tube following pleuroscopy or alternate pleural procedure preceding tube placement.

• Patient has already undergone a pleural procedure for the treatment of the pleural infection of interest (ex: prior chest tube placement or VATS with decortication).

# **Definitions**

A *complicated parapneumonic pleural effusion (CPPE)* is an effusion that has been infected with bacteria or other microorganisms (e.g., positive Gram stain or culture) or biochemical evidence of marked inflammation (e.g., low pH (<7.20), low glucose level (<60 mg/dl), and high lactate dehydrogenase (LDH)).

An *empyema* is a pleural effusion in which frank pus is aspirated from the pleural space.

A *blocked chest tube* is a chest tube that has stopped draining pleural fluid due to particulate material in the lumen of the tube.

A *successful chest tube removal* occurs when the infection in the pleural space has resolved as defined by clinical improvement of the patient and 24-hour fluid output from the chest tube of 150 mL or less.

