# **Study Procedure**

Patients will be eligible for randomization immediately following and up to 24 hours after chest tube placement. As per the standard of care, patients with a chest tube require a chest X-ray after chest tube placement to assess the proper position of the chest tube. Chest X-ray and ultrasound images obtained at the time of chest tube placement will be reviewed and their information documented as baseline/ day 1. The study team will obtain a baseline assessment of the pleural effusion via ultrasound if no ultrasound images are available within 24 hours prior to chest tube placement).

Subjects will be randomly allocated into intervention (regular flushing) and control (standard of care/flush as needed) groups using computer-generated randomization just prior to starting the procedure.

The intervention groups will have sterile saline 20 mL flushed into their catheter by trained nurses or study team members every 6 ± 2 hours. If patients are receiving tPA/DNase (combined at the same time), each treatment will be considered one flush.

The control groups will have no saline routinely instilled into the chest tube. Instead, chest tube patency will be assessed at least once/day. If the chest tube is considered blocked (lack of tidaling, lack of fluid drainage, and presence of fluid on US exam), the chest tube will be flushed with 20 mL of saline if indicated. All patients in both arms will have -20 cm H2O at the atrium (-80 cm H2O at the wall) continuous suction applied to their drainage system at all times if tolerated.

A daily checklist will be completed by the research team to assess for chest tube blockages and ongoing need for the tube/potential removal of the catheter (see CRF).

On the day of chest tube removal, both the intervention group and control group will undergo a repeat chest X-ray. Post-chest tube removal ultrasound images will be obtained by the research team. Chest X-rays can be performed as portable semi-erect or PA and lateral based on the clinical judgment of the primary provider.

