# **Outcomes**

Primary outcome: time from randomization (within 24 hours of chest tube placement) until time to chest tube removal (hours).

Secondary outcomes:

1 – length of hospitalization.

2 – radiographic improvement as evidenced by chest x-ray at the time of chest tube placement compared to the time of removal.

3 – additional surgical procedures for the management of pleural space infection (VATS, additional drains, etc.).

4 – Complications.

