# **Data Collection**

The following data will be collected from the records:

1) Demographic data – age, gender, race, smoking status

2) Indication for chest tube placement

3) Date and time of catheter placement

4) Amount of daily fluid drained while in place

5) Imaging data (Chest x-ray and ultrasound images)

6) Length of hospitalization

7) Any instances of deviations from an assigned group (e.g. if a drain was thought clogged and

underwent saline flushing outside of the protocol)

8) Replacement of catheter secondary to dislodgement or inability to drain

9) Presence or absence of continuous wall suction application (for >75% of the previous 24 hours)

10) Date and time of catheter removal

11) Data related to daily chest tube blockage assessment and chest tube removal objective data.

(Because the study investigators and participants are not blinded to the study arm, specific objective criteria (see CRF) for chest tube removal due to successful pleural space infection management will be assessed on daily bases. These data will be documented to assess for change in the behavior of provider due to lack of blinding. This includes categorization of daily drain status, meeting either “successful,” “ongoing” or “”failed criteria.” This data will be used to perform sensitivity analysis to address the potential effects of blinding. Research team members will capture this data.

13) Imaging data on day of chest drain removal (ultrasound, chest-X-ray, or CT scan) characterizing effusion status (Table 2).

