Previous studies have shown a varying number of days to chest tube removal based on etiology, with a mean of 7.6 days (SD: 1.53) in no regular flush populations in a study of 98 patients with infected pleural space (Cafarotti). There is limited data with only one small study reporting median days to chest tube removal (5 days (3-7) in a study of 36 patients with no-flush strategy) (Horsley). Assuming a non-normal distribution, with data skewed to the right, we estimated a median of 6 days to chest tube removal. Assuming a difference of 1 day (24 hours), earlier chest tube removal in the intervention (6 days in the SOC group and 5 days in the intervention group) is a clinical meaningful difference to detect. The sample size is calculated from a two-sided Wilcoxon Rank-Sum test at a 0.050 significance level with a standard deviation of 1.5. Group sample sizes of 38 in each arm achieve 80% power to detect a median difference of 1. The sample size estimation is based on a 2000 Monte Carlo simulation assuming samples from a range of distribution such as Gamma, Lognormal, and Gumbel distributions. Assuming a 10% withdrawal rate and 15% intrapleural enzyme therapy failure (which can prevent reaching the primary endpoint), we plan to enroll 96 Participants (with randomization performed in a 1:1 ratio). To avoid an unbalance in randomization among groups, randomization will be stratified by intrapleural enzyme therapy use.

The main analysis for the outcome will be performed according to the intention-to-treat principle; all the participants with an observed outcome will be included in the analysis according to their assigned trial group.

*Analysis plans*

Continuous variables will be summarized using the mean (SD) or median (range), as appropriate. Frequencies and percentages will be used to summarize categorical variables. The student t-test or the Wilcoxon test will be used to compare continuous variables between two different groups. The chi-square test or Fisher’s exact test will be applied to assess the association between two categorical variables such as complications by treatment.

The Wilcoxon rank sum test will be used to compare time from randomization (within 24 hours of chest tube placement) until time to chest tube removal between two arms among patients who achieved successful chest tube removal.

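### The 150 mL output criterion for successful removal does not exclude instilled saline, and scheduled saline goes to the flushing arm only

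*Protocol*

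**What the plan says.** The Definitions section requires two things for a successful removal: clinical improvement and a "24-hour fluid output from the chest tube of 150 mL or less". It calls the output neither gross nor net.

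Under Study Procedure, the intervention arm has "sterile saline 20 mL flushed into their catheter by trained nurses or study team members every 6 ± 2 hours". For controls, "The control groups will have no saline routinely instilled into the chest tube"; if the tube is judged blocked, "the chest tube will be flushed with 20 mL of saline if indicated". When tPA/DNase is given, "each treatment will be considered one flush". Both arms are on continuous suction if tolerated.

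Data Collection item 4 is "Amount of daily fluid drained while in place". No item asks for the volume instilled. Item 7 covers departures from the assigned arm, such as a flush outside the protocol, and is not a log of scheduled flushes. Item 11 has the research team grade each day as successful, ongoing or failed, using criteria held in the CRF, to support a sensitivity analysis for the lack of blinding.

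The primary outcome is time from randomization to tube removal, in hours. Statistical Considerations compares it "between two arms among patients who achieved successful chest tube removal".

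**The concern.** The criterion measures what comes out of the tube, and the randomized treatment puts fluid into the same tube. If returned saline is counted, the same 150 mL means a different amount of pleural fluid in each arm. That is measurement error tied to treatment assignment.

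It can reach the primary result in two ways:

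- **Timing.** If the tube stays in until recorded output falls to 150 mL, flushed patients wait longer. This runs against flushing.
- **Selection.** If clinicians mentally subtract the saline and remove the tube anyway, there is no delay. But a flushed patient whose recorded output was 160 mL, 80 mL of it saline, does not meet the written definition and leaves the analysis set, while a control draining 150 mL of pleural fluid stays in. If the patients lost this way are mainly early removals, this also runs against flushing.

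If the CRF uses the same criterion for the daily status, the sensitivity analysis meant to guard against open-label bias carries the same error and cannot reveal it.

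**Working it through.** **The plan's own figure.** Statistical Considerations gives 38 per arm for 80% power (two-sided 0.05, Wilcoxon, medians 6 and 5 days, SD 1.5). Two means: 2 × (1.960 + 0.842)² × 1.5² / 1² = 35.3, rounded up to 36. Times π/3 for the rank test gives 37.7, so 38. Simulation at 38 per arm gives power 0.805 (normal), 0.803 (gamma), 0.825 (lognormal) and 0.872 (Gumbel). The figure reproduces and is not in dispute. It fixes the yardstick: a 1-day effect.

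**Scheduled saline.** Daily volume = 20 mL × 24 / interval in hours. Pleural fluid allowed at the criterion = 150 − (returned fraction × daily volume). The return fraction is not in the protocol, so full and half return are assumptions.

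| Interval | Saline per day | Share of 150 mL | Pleural fluid allowed, full return | Half return |
|---|---|---|---|---|
| 8 h | 60 mL | 40% | 90 mL | 120 mL |
| 6 h | 80 mL | 53% | 70 mL | 110 mL |
| 4 h | 120 mL | 80% | 30 mL | 90 mL |
| Control, no flush | 0 mL | 0% | 150 mL | 150 mL |

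**Things that narrow the gap.** A control given one as-needed flush has 20 mL instilled, leaving a gap of 80 − 20 = 60 mL at 6-hourly flushing. Each tPA/DNase treatment replaces one scheduled flush. With two treatments in a day (assumption), scheduled saline at 6-hourly flushing is 80 − 40 = 40 mL. The enzyme volume, which the protocol does not give, can enter either arm.

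**Possible delay.** The protocol does not say how fast output falls. Assume exponential decline with half-life h, and that the output criterion is the last one met. Then delay = h × log2(150 / pleural fluid allowed). At 80 mL a day:

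| Half-life | Full return: h × log2(150/70) | Half return: h × log2(150/110) |
|---|---|---|
| 0.5 d | 0.55 d | 0.22 d |
| 1 d | 1.10 d | 0.45 d |
| 2 d | 2.20 d | 0.89 d |

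With full return and a 1-day half-life, the ends of the flushing window give 0.74 d (60 mL) and 2.32 d (120 mL). Where clinical improvement is the later condition, the delay is zero.

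**Effect on power, for scale.** If the difference between arms shrank from 1 day to 0.5 day, simulated power at 38 per arm would fall from about 0.80 to about 0.30 (gamma or lognormal). At 0.75 day it would be 0.55 to 0.59.

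**The case against.** The strongest reply is that the protocol never says gross. The wording is silent, the objective removal criteria are referred to the CRF, and the CRF is not shown; it may already specify net output. This stands as a limit on certainty. It does not remove the point, because neither the protocol's definition nor its data list provides for a deduction, and the plain reading of unqualified output is what drains.

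Second, the primary outcome is actual removal, and no section makes 150 mL the trigger for it. A reader might infer that flushed patients are necessarily kept on drainage longer. The document does not support that: clinicians know the arm and may discount the saline. What then remains is the selection problem in the analysis set.

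Third, a reader might infer that the saline cancels the whole 1-day target effect. That needs full return and a 1-day half-life, neither of which is in the protocol, and it needs output to be the last condition met.

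Fourth, it would be too strong to say that only the flushing arm has fluid instilled. That is true of routine saline; as-needed flushes and enzyme treatment reduce the contrast.

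Fifth, a reader might take the daily successful/ongoing/failed status to use the 150 mL criterion. The Multistate Transition Model section defines treatment success without any volume, so the link depends on the CRF.

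**Conclusion.** The point holds in conditional form. As written, the criterion does not exclude instilled fluid, and the schedule gives one arm 60 to 120 mL a day (less on enzyme days), 40 to 80% of the 150 mL. To the extent that saline returns, a flushed patient must have less pleural fluid than a control to count as a success: 70 against 150 mL at 6-hourly flushing with full return, 110 mL with half return. Whether this acts through later removal or through exclusion from the successful-removal set, it biases the primary comparison.

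The inequality follows from the text plus some return of saline. The size of any delay does not: it runs from zero to about 2.2 days at 80 mL a day, with 0.2 days at the low end of the assumed cases where output is the deciding condition. That range includes the 1-day effect the trial is sized to detect, so it should not be left to chance.

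**What to change.** For endpoint classification and for the daily status, define 24-hour output as volume drained minus all volume instilled through the tube in the same 24 hours (scheduled flushes, as-needed flushes and tPA/DNase), worded identically for both arms. Add daily instilled volume to item 4 of Data Collection. The sponsor should reconcile Definitions, Study Procedure, Data Collection and the CRF on this. If the CRF already specifies net output, the protocol needs one sentence saying so.

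The 150 mL threshold, the flush schedule and the bedside decision to remove a tube are not touched and stay with the sponsor.

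The cost is one definition and one extra CRF field. For patients already enrolled, the correction is possible only where actual flush records exist. The schedule cannot stand in for them, because the ± 2 hour window alone lets the daily volume vary from 60 to 120 mL.
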